As mentioned previously, we will also enroll women referred to the study if they meet all eligibility criteria. During our formative research we have learned that it is very common for information about programs offered throughout the camp to be spread by word-of-mouth. We would like to allow women in Nyarugusu that are eligible for the study, but not part of a women’s group to be able to participate. Thus, if a woman does learn about the study and elects to invite a woman that she knows and think could benefit to an assessment appointment, we will not exclude her. Women that engage with the study in this manner will undergo the same consent, screening, assessment and intervention procedures as women recruited through women’s groups. However, we do anticipate recruiting the majority of our participants from women’s groups as these are our primary recruitment source. To protect the privacy and safety of women in Nyarugusu, we will not be advertising or providing study contact information to anyone besides the study participants and staff/investigators.

*Process Evaluation:* Participants in the process evaluation will be approached by members of the research team and asked if they would be willing to conduct an interview regarding the Nguvu program with a focus on experiences with and recommendations for implementation. The 10 participants from the Nguvu trial will be randomly selected using a blocked design based on Nguvu intervention attendance. The remaining participants will be identified by study staff based on their roles in the Nguvu program or a particular partner agency. All participants must provide oral consent prior to proceeding with the interview.

2. Address any privacy issues associated with recruitment. If recruitment itself may put potential participants at risk (if study topic is sensitive, or study population may be stigmatized), explain how you will minimize these risks.

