Randomization and Intervention: Given that this is a cluster-randomized trial, the randomization of women’s groups (unit of randomization) will occur prior to recruiting any participants. Thus, if a participant completes the baseline assessment, the intervention team (which works independently from the research team) will identify whether that person belongs to a women’s group that has been randomized to the intervention (vs. control) condition. If in the intervention group, a member of the intervention team will make contact with the participant and schedule their first intervention session. There will be eight sessions that take place once per week for eight weeks.

Follow-up Interview: The week following the intervention, the participant is then asked to complete a follow-up interview. If the participant belongs to a control women’s group then all procedures, with the exception of the intervention, will be the same.

Process Evaluation: A subset of participants will participate in a qualitative process evaluation. In addition to this subset, members of the research and intervention team as well as representatives from partner agencies will be recruited to provide their experience with the implementation of Nguvu.

Responsibilities of the Research and Intervention Personnel: As mentioned above (in Randomization and Intervention), the research assistants and intervention facilitators are expected to work independently to preserve blinding of research assistants to participant’s study assignment. Thus, the research and intervention teams are managed separately with Muhimbili University of Health and Allied Sciences (co-investigators [name] and [name]) responsible for managing the research team and the International Rescue Committee (co-investigator [name]) responsible for managing the intervention team. Johns Hopkins (principal investigator [name]) is responsible for overseeing management across both teams and coordinating their activities. A summary of activities and which teams are responsible for implementation of these activities throughout the duration of the study is displayed below.

| **Study Activity (in chronological order)** | **JHU** | **MUHAS** | **IRC** |
| --- | --- | --- | --- |
| Randomization of women’s groups | X |  |  |
| Recruitment of participants |  | X |  |
| Screening of participants |  | X |  |
| Baseline assessment |  | X |  |

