| Identifying study assignment (based on participant’s women’s group affiliation indicated in baseline assessment) |  |  | X |
| Intervention sessions 1-8 |  |  | X |
| Post-intervention assessment |  | X |  |
| Participant retention (in intervention, intervention group only) |  |  | X |
| Participant retention (assessments, intervention and control group) |  | X |  |
| Process evaluation |  | X |  |
| Analysis and dissemination | X |  |  |
| Coordination of activities | X |  |  |

JHU: Johns Hopkins, MUHAS: Muhimbili University of Health and Allied Sciences, IRC: International Rescue Committee

1. Describe the number and type of study visits and/or contacts between the study team and the participant, how long they will last, and where/how they will take place.

Research Study Visits: All participants will complete 2-4 research study visits: screening/baseline which may take place in a single or two separate study visits, a post-intervention interview and possibly, if randomly selected, a qualitative process evaluation interview. The screening is estimated to take approximately 20-30 minutes. The baseline and post-intervention interview are estimated to take approximately 1.5 hours. The qualitative process evaluation is estimated to take between 45-60 minutes. All research visits will take place either at the research team office, which is located in the International Rescue Committee education center in the camp, or at a private location of the participant’s choice. Participants randomized to the intervention will also have 8 intervention visits. Intervention visits last anywhere from 1.5-2 hours each and will take place at existing International Rescue Committee private meeting spaces in the camp.

In addition to the regular study visits, a random 10% of participants will be contacted by the research team leader to confirm that the research assessments took place as intended for quality assurance and data collection monitoring purposes. The research team leader will contact selected participants preferably by phone, or in person if they are unreachable, and ask them the following questions:

1. Did a member of the study team complete the scheduled research assessment?
2. Approximately how long did the assessment last?
3. What was the name of the research assistant that conducted the interview?

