The proposed study is cluster-randomized with women’s groups in the camp being defined as the clusters. Thus, randomization of women’s groups will occur before recruitment and data collection begin. The women’s groups in the camp will be randomized to intervention versus control by a faculty member in the Department of Mental Health at Johns Hopkins that has had no contact with the research field team (research assistants, in-country project coordinator). This independent faculty member will use a random allocation sequence generated by statistical software, which will remain with that independent JHSPH faculty member in Baltimore, not accessible to the research and intervention teams in Tanzania. All participants that are eligible and consent for enrollment will be asked to provide their address in the camp. Their study assignment will be determined by whether they reside in an intervention or control women’s group. The research assistants will be blind to study assignment. The in-country project coordinator, who does not conduct any data collection, will be responsible for coordinating communication with the intervention team to schedule sessions with enrolled participants belonging to intervention clusters. The process and timeline of conducting research study visits is the same between groups and will be managed by the research team.

- 1. If human biospecimens (blood, urine, saliva, etc.) will be collected, provide details about who will collect the specimen, the volume (ml) and frequency of collection, how the specimen will be used, stored, identified, and disposed of when the study is over. If specimens will be collected for use in future research (beyond this study), complete the Biospecimen Repository section below.

N/A

- 1. If genetic/genomic analyses are planned, address whether the data will be contributed to a GWAS or other large dataset. Address returning unanticipated incidental genetic findings to study participants.

N/A

- 1. If clinical or laboratory work will be performed at JHU/JHH, provide the JH Biosafety Registration Number.

N/A

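### Referred women who belong to no women's group are enrolled, but the conflicting assignment rules give them neither a randomised arm nor a cluster

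*Protocol*

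**What the plan says.** **Unit and timing of randomisation.** Section V.C, Randomization and Intervention, states that "the randomization of women’s groups (unit of randomization) will occur prior to recruiting any participants". Section III (Aim 3) and section V.C.6.a also make the women's group the unit.

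**Who may enter.** Section V.A, item 1, adds a referral route. Referred women need not be in any group: the investigators want women "that are eligible for the study, but not part of a women’s group to be able to participate". If a woman who has heard of the study "elects to invite a woman that she knows and think could benefit to an assessment appointment, we will not exclude her". Referred women "will undergo the same consent, screening, assessment and intervention procedures as women recruited through women’s groups". No cap is set. The protocol says only that it expects most participants to come from women's groups.

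**How an arm is assigned.** The rule appears three times:
- Section V.C, Randomization and Intervention: after baseline, the intervention team "will identify whether that person belongs to a women’s group that has been randomized to the intervention (vs. control) condition". It contacts the woman if so.
- Activity table in the same section: assignment is identified "based on participant’s women’s group affiliation indicated in baseline assessment".
- Section V.C.6.a: each enrolled woman gives her camp address, and then "Their study assignment will be determined by whether they reside in an intervention or control women’s group".

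**Analysis.** The data analysis plan in section V.C specifies multilevel mixed models with clustering by women's group.

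**The concern.** In a cluster-randomised trial a participant has a randomised arm only through her cluster. Here the protocol deliberately enrols women who have no cluster, and then assigns arms by rules that all presuppose one. Two of those rules use membership and the third uses residence, so they also disagree with each other.

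Two things are at stake. The first is allocation. Any arm given to a non-member without a pre-specified link to a randomised group is not a random one, and no later analysis can make it so. The second is the model: a woman in no group has no level of the women's-group term. How she is then modelled could be left to a SAP, but a SAP cannot supply an allocation that was never made.

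The referral route adds a further exposure. Groups are randomised before recruitment, and section V.C.6.g accepts that participants cannot be blinded. An enrolled woman who knows her arm could therefore be the one who invites a friend.

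**Working it through.** **1. Apply each rule to a referred woman who is in no group.**

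| Place in the protocol | Criterion | Result for a non-member |
|---|---|---|
| V.C, Randomization and Intervention | Belongs to a randomised group | No group, so not identified as intervention and not contacted |
| V.C, activity table | Group affiliation recorded at baseline | None to record |
| V.C.6.a | Resides in an intervention or control group, after an address is taken | Undefined: a group is not a place |
| V.A, item 1 | Same procedures as group members | No rule of its own |

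**2. Can the address close the gap?** It would need a map from address to randomised group.
- Section IV describes the groups as cooking, weaving, tailoring and microfinance groups of roughly 11–20 women.
- Section III says they operate within the camp's 52 villages, but it is the group that is randomised, not the village.
- The protocol neither maps an address or village to one group nor says that groups in the same village share an arm. The address therefore does not determine an arm. For a woman who is in a group, it could also disagree with her membership.

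**3. What happens if the text is followed literally?** The intervention team contacts only women in intervention groups, so every non-member goes without the intervention. Her arm is then decided by not belonging to a group, which is a characteristic of the woman and not the outcome of randomisation.

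**4. How many women?** The share is not stated. Assume 5–20% of the target of 360:
- 0.05 × 360 = 18
- 0.20 × 360 = 72

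The only limit in the text is that a majority is expected from groups. At an assumed 49% the count would be 0.49 × 360 ≈ 176.

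**5. What would leaving them out cost in power?** The protocol's own figure (section III, sample size) reproduces first:
- Unadjusted n per group = 2 × (1.96 + 0.842)² × 0.55007 / 0.6² = 23.99
- Design effect = 1 + (18.269 − 1) × 0.333 = 6.751
- 23.99 × 6.751 = 161.97, rounded to 162; 162 / 0.90 = 180 per group

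This uses the cluster size in the worked formula. The listed m = 10 would give 95.9 per group, which is a separate matter.

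Now let a fraction f of the 162 be non-members who are left out and not replaced. Power = Φ(0.6 / √(2 × 0.55007 × DE / n) − 1.96), with n = 162 × (1 − f):

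| f (assumed) | DE held at 6.751 | Cluster size shrinks in proportion |
|---|---|---|
| 0 | 80% | 80% |
| 10% | 75.8% | 79.6% |
| 20% | 70.8% | 79.1% |

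The second column of results applies if the non-members would otherwise have been counted in existing groups. Power is the lesser issue; the defect is in the allocation.

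**The case against.** The best defence is section V.C.6.a. It covers every eligible, consenting woman, takes her address, and speaks of where she resides. With groups operating inside villages, this suggests that the investigators meant to assign by location, which could reach women in no group. That much stands: the text does not show that no rule was intended. But the rule is written in terms of groups, has no map behind it, and conflicts with the membership rule stated twice elsewhere.

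It can also be said that the handling of non-members in the random-effects model belongs in a SAP. That is fair for the model but not for the assignment rule, which the protocol itself sets.

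A reader might infer more than the documents support:
- **That the intervention team picks the arm of referred women.** The text has that team identify assignment, not choose it. The literal result is that non-members are not contacted.
- **That women in two groups have two arms.** The protocol does not say that anyone belongs to more than one group.
- **That referrers are enrolled women who know their arm.** Section V.A says only that the referrer has learned of the study. She may be unenrolled, or may have heard of it before any arm was known. Study contact details go to participants and staff, so an informed referrer is possible, but not stated. That control women would have less reason to refer is speculation.
- **That a bias can be quantified.** This would need the share of non-members in each arm and the outcome difference between them and members, and the protocol gives neither. A difference in post-intervention level also cannot simply be set against the planned 0.6: the sample-size formula uses the variance of change, so 0.6 reads as a difference in mean change.

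**Conclusion.** The concern holds as a conflict and gap in the allocation rule. The protocol enrols women in no group, assigns arms in one place by membership and in another by residence in a group, and under neither wording gives a non-member a randomised arm or a cluster. Followed literally, the membership rule puts all non-members on the untreated side, which is non-random allocation inside a randomised comparison.

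About 18–72 of 360 women are affected if 5–20% are non-members. That share is an assumption, because the protocol states only an expected majority from groups. The size and direction of any bias are unknown. Referral by a woman who knows her arm is a possibility the protocol leaves open, not something it describes. The point needs settling before recruitment, because an allocation cannot be repaired after enrolment.

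**What to change.** Replace the wording in section V.A (referral), section V.C (Randomization and Intervention, and the activity table) and section V.C.6.a with one rule, fixed before recruitment starts. Each woman is assigned to the women's group through which she was recruited and is analysed in that cluster. Remove the residence wording in V.C.6.a or reconcile it with this rule.

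For referred women in no group, choose one option in advance:
- **(a)** Leave them out of the randomised primary comparison and report them separately.
- **(b)** Assign them by a pre-specified link to one randomised group, for example the inviting woman's group, recorded before screening, and analyse them in that cluster. Leave out women whose referrer has no group. Run a sensitivity analysis restricted to group members.

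Under (b), any referral cut-off should follow the same schedule in both arms. A cut-off tied to when a group's allocation becomes known would not work: the protocol defines no such date for control groups, so it could differ by arm and could unblind the assessors who do the screening.

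The cost is a short amendment and one field on the screening form. Under (a), and for women left out under (b), fewer women count toward the 360. They would have to be replaced, or the loss of power shown above accepted.

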We plan to conduct a cluster randomized controlled trial evaluating the efficacy of the aforementioned integrated mental health treatment and intimate partner violence prevention intervention as compared with a treatment as usual control group. In Nyarugusu Refugee Camp, the setting of this study, there are 7 zones within which refugees live. These zones are further subdivided into 52 villages. Women’s groups (described in further detail below; section IV. Participants) operate within these villages and will serve as the site of recruitment and the unit of randomization. Women entering the trial will be assessed for symptoms of mental health problems, intimate partner violence and other related constructs at baseline (week 1) and one post-intervention follow-up at week 10. All measurement and data collection is based on self-report indicators reported by the participant. The intervention is designed to last approximately 2 months (8 sessions, once per week for 8 weeks) with full participation in the study lasting 10 weeks (baseline to follow-up).

AIM 4: Conduct a qualitative process evaluation to examine facilitators and barriers to implementation of the research and intervention protocols.

We plan to conduct a qualitative process evaluation of the implementation of the Nguvu intervention and research protocols within the context of the randomized controlled trial described in Aim 3. To do so we will recruit a subset of participants (n=10), both high (n=5) and low attenders (n=5) from the intervention condition to participate in a qualitative interview with a member of the research team to discuss their experience participating in the intervention related to perceived challenges, risks, benefits, operations and acceptability. We will also qualitatively interview the 10 intervention facilitators and their clinical supervisor to identify their perspectives on successes and challenges of the intervention as well as their experiences as a provider of these services. Lastly, we will conduct qualitative interviews with seven representatives from partner agencies and the community advisory board to examine structural challenges to implementation as well as the perceived impact that implementing Nguvu had at the community and organizational level. We estimate that each of these interviews will take approximately one hour to complete and will be delivered by our trained research assistant team.

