1. Provide a sample size and a justification as to how you arrived at that number. If you use screening procedures to arrive at a final sample a table may be helpful.

Pilot Study:

We have chosen to include 60 women in the measurement validation and pilot intervention phase because this sample size will allow for each pair of facilitators (5 pairs in total) to run through the entire intervention starting with 12 women each. Sixty participants is also a sufficient sample size to meet the objectives of our measurement validation activities.

Randomized Controlled Trial:

Our primary outcomes are both assessed on a continuous scale, thus we conducted a sample size calculation for the randomized controlled trial intended for two-sample mean comparisons using one of our primary outcomes of interest, psychological distress. We gathered information from previous trials measuring our primary outcome(s) of interest in similar populations to estimate the following parameters used for the sample size calculation:

$$\sigma_{time1}^{2}=0.25$$

$$\sigma_{time2}^{2}=0.36$$

$$\rho=0.333$$

$$\sigma_{change}^{2}=0.55007$$

$$m=10$$

$$\mu_{1}=1.3$$

$$\mu_{2}=0.7$$

$$N=\frac{2\left( z_{\frac{\alpha}{2}}+z_{\beta} \right)^{2}(\sigma^{2})(1+\left( m-1 \right)\rho)}{{(\mu_{1}-\mu_{2})}^{2}}=\frac{2\left( 1.96+0.842 \right)^{2}(0.55007)(1+\left( 18.269-1 \right)0.333)}{{(1.3-0.7)}^{2}}=161.97$$

In order to have 80% power to detect a treatment effect of similar magnitude as previous trials that are roughly comparable in terms of intervention and population at the 0.05 significance level, we need 162 persons per group. To account for 10% attrition, we will recruit a target sample of 180 participants per group (360 total).

Process Evaluation:

We will conduct a total of 28 qualitative interviews as part of the process evaluation. We will recruit a subset of the participants that were enrolled in the randomized controlled trial (n=10) to participate in the process evaluation. We will recruit 10 intervention facilitators, their clinical supervisor (n=1) and 7 members of local partner organization to interview regarding implementation facilitators and challenges. These new participants will not be interviewed regarding personal health information and the focus of the interviews will be on program implementation.

Total Sample Size:

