
Baseline assessment

*Process Evaluation (Oral Consent)*

All participants included in the process evaluation must provide oral consent to a member of the research team. The consent discussion will occur in a private place unless the participant requests otherwise and is comfortable discussing the themes of the process evaluation, which do not include personal or sensitive health information, in a public setting. The oral consent describes the purpose of the process evaluation, potential risks and benefits of participating, and protections for the patient (e.g. confidentiality, autonomy). The process evaluation is estimated to take 45-60 minutes and is in the form of an unstructured interview.

2. Identify the countries where the research will take place, and the languages that will be used for the consent process.

| Country | Consent Document(s)  (adult consent, parental permission, youth assent, etc.) | Languages |
| --- | --- | --- |
| Tanzania | Oral consent (screening) | Kiswahili |
| Tanzania | Written consent (enrollment) | Kiswahili |
| Tanzania | Oral consent (process evaluation) | Kiswahili |

*Note:* Congolese refugees in Tanzania speak Kiswahili, French and, in fewer cases, English. Kiswahili tends to be the language commonly spoken and it has developed into a hybrid form of Kiswahili incorporating elements of Tanzanian and Congolese Kiswahili. We have spent substantial time working with the research team and translators from Muhimbili University of Health and Allied Sciences (MUHAS) to adapt and translate our measures and consent form such that they reflect this type of Kiswahili (see certificate of translation).

C. Study Implementation:

Answer the following:

1. Describe the procedures that participants will undergo. If complex, insert a table below to help the reviewer navigate.

Recruitment and Screening: Contact with participants begins at recruitment. Participants will be recruited from women’s groups or on a referral basis at which time they will be invited to participate in a screening interview, which is preceded by an oral consent process.

Enrollment and Baseline Interview: If eligible, the research assistant then seeks written consent for enrollment followed by the baseline interview, which may directly follow screening or be rescheduled for another time in the upcoming week.

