There are also safety risks related to participating in the study. There is the potential that someone (e.g. a husband/partner, family member) may find out that a woman is participating in the Nguvu intervention and furthermore that the Nguvu intervention is an intervention targeting women experiencing intimate partner violence in the past year. This might be aggravating to a husband/partner or other person that may have been the perpetrator of this violence or other community members that may see participating as disrespectful to the woman’s relationship. To minimize these risks we have designed the study in such a way that recruitment, interview and intervention sites are all in neutral locations that are common for women to frequent or in a private place where the woman feels comfortable – so that suspicion is not raised. Moreover, intervention facilitators and research assistants review participant’s safety during intervention sessions and research assessments respectively. We also provide both the intervention and control participants with a resource map/referral chart that includes contact information for agencies in case of emergencies as well as to receive other intimate partner violence response services – so that in effect, the study will increase safety and safety monitoring of respondents.

1. Describe the anticipated frequency and severity of the harms associated with the risks identified above; for example, if you are performing “x” test/assessment, or dispensing “y” drug, how often do you expect an “anticipated” adverse reaction to occur in a study participant, and how severe do you expect that reaction to be?

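### The on-request public setting in the process-evaluation consent rule covers all 28 interviewees, and for the ten trial women it does not fit the protocol's own private-location rule

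*Protocol*

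**What the plan says.** Four places in the protocol bear on this.

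- **Section V.B, Consent Process, Process Evaluation (Oral Consent).** The rule is: "The consent discussion will occur in a private place unless the participant requests otherwise and is comfortable discussing the themes of the process evaluation". The sentence goes on to describe those "themes of the process evaluation, which do not include personal or sensitive health information, in a public setting". It makes no distinction between kinds of interviewee.
- **Section V.C, Research Study Visits.** For trial participants, the list of visits includes "a post-intervention interview and possibly, if randomly selected, a qualitative process evaluation interview". The location rule follows: "All research visits will take place either at the research team office", "or at a private location of the participant’s choice". No public option is given.
- **Section III.** Under Aim 4, the women sampled from the intervention arm are to "discuss their experience participating in the intervention related to perceived challenges, risks, benefits, operations and acceptability". Under Process Evaluation in the sample-size part, after the facilitators, their supervisor and the partner-organisation members have been listed, the text says: "These new participants will not be interviewed regarding personal health information".
- **Section VII, Risks of the Study.** A partner, relative or other person "may find out that a woman is participating in the Nguvu intervention", and may also learn that the programme is aimed at women with recent IPV. The protocol says this could aggravate a perpetrator.

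**The concern.** The reason given for allowing a public setting is that the themes are neither personal nor sensitive. That fits staff and partner-agency representatives, who speak about programme delivery. It is not shown to fit the ten trial women. Section IV says they meet the trial's eligibility criteria, so each has a past-year history of IPV and moderate to severe psychological distress. They are asked about risks and benefits they perceived in a programme that, according to Table 1 in section V.C, contains IPV information, a danger assessment and safety planning.

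What is at stake is participant safety rather than inference. A consent discussion covers the purpose, risks and benefits of the evaluation, so being overheard at that stage could already contribute to someone learning that the woman takes part. Field staff also have two rules for the same ten women, one allowing a public place on request and one requiring a private place, and nothing says which applies.

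**Working it through.** No sample size, power or error rate is involved. The check is a count followed by a comparison of texts.

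**1. Who is interviewed.** The sample-size part of section III gives 10 trial participants + 10 facilitators + 1 clinical supervisor + 7 others = 28, which reproduces the stated total. The list of non-client interviewees in section IV gives 10 + 1 + 1 + 1 + 2 + 1 + 2 = 18. Then 28 − 18 = 10 trial women (5 high and 5 low attenders), or 10/28 ≈ 36% of the interviews.

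**2. The setting rules for those ten women.**

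| Point | Section V.B (process-evaluation consent) | Section V.C (research visits) |
| --- | --- | --- |
| What the rule governs | The consent discussion; the themes are mentioned as something that might be discussed in public | All research visits, with the process-evaluation interview listed among them |
| Default | Private | Office or private location |
| Participant's choice | May ask for a public setting, if comfortable | May choose the place, but it must be private |
| Public setting allowed | Yes, on request | No |

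If consent is taken at the start of the interview visit, the two rules give different answers when a woman asks for a public place. If consent is taken separately, section V.B alone governs that discussion, and its wording still contemplates talk of the evaluation's themes in public.

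**3. The stated reason.** Section V.B applies the not-personal-or-sensitive description to the whole process evaluation. Section III makes its statement about personal health information for the new participants only, that is, for the 18. The two statements differ in scope, and the difference is exactly the ten trial women. Section V.B also calls the interview unstructured, so the protocol fixes no question list that would keep personal material out.

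**4. Comparison with the trial's own screening consent.** The screening consent in section V.B also lets a woman ask for a different place, but that place must be private. The process-evaluation consent is therefore looser for women already enrolled as IPV survivors than the screening consent is for women not yet screened.

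**5. Link to the named risk.** Section VII relies on neutral sites that women commonly visit, or on private places, to avoid suspicion. It therefore does not demand privacy everywhere. It supplies the hazard; the mismatch of rules is with sections V.C and III.

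**The case against.** The case on the other side has real force.

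- **The exception is narrow.** Private is the default, and a public setting needs both the participant's own request and her comfort. This stands, and it limits exposure to women who ask. It does not settle the mismatch, because section V.C already respects her choice of place and still requires privacy.
- **The sentence is about consent, not the interview.** A reader might infer that the protocol allows the interview itself to be held in public. The text does not say so: the subject of the sentence is the consent discussion, and section V.C can be read as already protecting the interview. This stands. What remains is the consent discussion and a clause about discussing themes in public that sits badly beside section V.C.
- **The interview topics may not be sensitive.** Section V.A describes a focus on experiences with implementation and recommendations for it, and nothing says the women will be asked for violence or health histories. Attendance is how they are sampled, not a listed topic. So the description in section V.B is not shown to be false for them. Equally, it is not shown to be true, and section III stops short of saying it.
- **The harm can be overstated.** A reader might infer that being overheard would by itself expose a woman as an IPV survivor, or that the protocol names partner retaliation. Neither is supported. Section VII describes two steps, learning that she participates and learning what the programme targets, and says only that discovery might aggravate a partner or other person. Section VII also says the study is designed so that recognition as an IPV programme is highly unlikely.
- **Less candid answers.** A reader might expect a public setting to make answers less frank. That is plausible, but nothing in the protocol documents it, and the woman would have chosen the setting.

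**Conclusion.** The point holds as a consistency problem with a modest safety consequence. Section V.B extends an on-request public setting, and the reason given for it, to all 28 interviewees. For the ten intervention-arm women this does not fit the office-or-private rule in section V.C or the narrower assurance in section III.

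Its size is bounded above by 10 of 28 interviews. The number actually exposed is the number of women who request a public setting, which the protocol does not give and which could be zero. The probability of disclosure cannot be estimated from the document.

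The conclusion rests on two readings: that the process-evaluation interview of a trial woman is a research visit, as section V.C lists it, and that the new participants in section III are the 18 non-clients. Both follow from the text. It does not rest on the interview itself being held in public.

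Priority is minor. No randomised comparison, primary outcome, sample size or timeline is affected.

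**What to change.** In section V.B, under Process Evaluation (Oral Consent), limit the public-setting option, and the statement that the themes are not personal or sensitive, to the 18 staff and partner interviewees. For the ten trial women, state that the office-or-private-location rule of section V.C applies to both the consent discussion and the interview. Check that the oral consent script, which is not in the document reviewed, agrees with the revised wording.

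The cost is a sentence or two in the protocol and, if needed, in the script. The private office already exists. The one downside is that these ten women lose the option of a public setting, but each may still choose any private location.
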